### Respiratory Therapy Intervention

According to the Respiratory Therapy care model in the ICU of the Hospital Universitario de la Fundación Santafé de Bogotá (FSFB), a patient begins intervention when the attending physician requests a consultation with Respiratory Therapy. Respiratory therapists conduct the evaluation and initiate the treatment plan.

As part of the SECEC-2023-129 project, there will be two intervention groups: early multimodal therapy and late multimodal therapy. Early Multimodal Therapy: This will be initiated within the first 24 hours following the intubation of a patient in the ICU. Late Multimodal Therapy: This will be initiated according to the Respiratory Therapy care model for critically ill patients at the Fundación Santa Fe de Bogotá, i.e., when the attending physician requests a consultation with Respiratory Therapy.

Regardless of the group to which the patient is assigned, 3 sessions will be conducted daily (morning, afternoon, and night) seven days a week, with each session lasting:

Dividing into 3 big categories:

- Techniques of permeabilization of the airway
- Techniques of re-expansion pulmonary
- Techniques of strengthening muscular respiratory

| INTERVENTION | DURATION OF THE SESSION |
|--------------|-------------------------|
|--------------|-------------------------|

|                                                                                          |            |
|------------------------------------------------------------------------------------------|------------|
| PATIENT LOW VENTILATION MECHANICS INVASIVE                                        |            |
| Suction of secretions by tube endotracheal                                               | 3 minutes  |
| Suction of secretions oropharyngeal + Hygiene of cavity oral                             | 5 minutes  |
| Bronchial hygiene technique using flows expiratory in ventilation mechanics              | 15 minutes |
| muscle training diaphragmatic in a patient ventilated by half of the trigger by pressure | 5 minutes  |
| Time total employee: 28 minutes                                                   |            |
| PATIENT ALREADY WITHOUT VENTILATION MECHANICS INVASIVE                            |            |
| Exercises diaphragmatic in patients without ventilation mechanics                        | 5 minutes  |
| Exercises of ventilation-directed                                                        | 5 minutes  |
| Incentive respiratory                                                                    | 3 minutes  |
| Slow expiration techniques prolonged                                                     | 3 minutes  |
| Techniques of directed cough                                                             | 3 minutes  |

|                                                                  |           |
|------------------------------------------------------------------|-----------|
| Techniques of expiration forced                                  | 3 minutes |
| Utilization of assistance of cough either
COUGH ASSIST | 5 minutes |
| TIME TOTAL EMPLOYEE: 27 minutes                           |           |

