| Comparator | Late multimodal therapy is defined as the initiation of multimodal therapy 3 days or more after the start of mechanical ventilation. The comparator differs from the study intervention only in the moment (time from orotracheal intubation to the start of multimodal therapy) of initiation of therapy.                                                                                                                                                                                                                                                                                                                                                                                                                                                                                                                                                                                                                                                                                                                                      |
| Outcomes   | 
Effectiveness
 
Primary outcome: Number of days with invasive mechanical ventilation in the ICU
 
Secondary outcomes:
 
 
• Days free of mechanical ventilation until day 28
 
• Days of delirium until day 28
 
• Time in ICU with delirium until day 28
 
• Days of hospitalization with delirium until day 28
 
• Sedation days until day 28
 
• Sedation-free days until day 28
 
• Barthel index at discharge
 
• Days of hospital stay
 
• Length of stay in ICU
 
• Mortality from any cause up to 90 days
 
• Time from intubation to start of therapy
 
• Muscle strength measured with the medical research scale council (MRC)
 
• Dysphagia at 72 hours
 
• Time until initiation of oral administration
 
• Development of healthcare-associated pneumonia,
 
• Maximum mobility measured by JH-HLM
 
• Grip strength
 
• Extubation failure
 
 |

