### **Occupational Therapy Intervention**

According to the Occupational Therapy care model in the ICU of the Hospital Universitario de la Fundación Santafé de Bogotá (FSFB), a patient begins intervention when the attending physician requests a consultation with Occupational Therapy. Occupational therapists conduct the evaluation and initiate the treatment plan.

As part of the SECEC-2023-129 project, there will be two intervention groups: early multimodal therapy and late multimodal therapy. Early Multimodal Therapy and Late Multimodal Therapy: This will be initiated within the first 24 hours following the intubation of a patient in the ICU.

This will be initiated according to the standard management by occupational therapy in critical care at the Fundación Santa Fe de Bogotá, i.e., when the attending physician requests a consultation with Occupational Therapy.

Regardless of the group to which the patient is assigned, 1 session per day will be conducted for patients with a RASS score of -3 or lower. When weaning begins (RASS -2 to -1 or higher than +1), 2 sessions per day will be conducted, distributed in the morning and afternoon, seven days a week, with each session lasting 30 minutes.

Please specify the duration of each session and if the duration varies based on patient characteristics.

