### **Physiotherapeutic Intervention**

According to the Physiotherapy care model in the ICU of the Hospital Universitario de la Fundación Santafé de Bogotá (FSFB), a patient begins intervention when the attending physician requests a consultation with Physical Medicine and Rehabilitation (Physiatrist), who provides indications for Physiotherapy. Physiotherapists conduct the evaluation and initiate the treatment plan.

As part of the SECEC-2023-129 project, there will be two intervention groups: early multimodal therapy and late multimodal therapy. Early multimodal therapy will be initiated within the first 24 hours following the intubation of a patient in the ICU. Late multimodal therapy will be initiated

according to the Physiotherapy Intervention protocol for critically ill patients at the Fundación Santa Fe de Bogotá (Code: AMB-REHF-PT-020), i.e., when the attending physician requests a consultation with Physical Medicine and Rehabilitation.

Regardless of the group to which the patient is assigned, two sessions will be conducted daily (morning and afternoon) seven days a week, with each session lasting:

25-minute sessions:

- Patients with clinical conditions requiring ventilatory support, inotropic support, sedo-analgesia, and renal replacement therapy, require continuous supervision and longer recovery periods between exercises.

50-minute sessions:

- Sessions involving ambulation of a patient with invasive or non-invasive mechanical ventilation (mobilization of multiple equipment and coordination of the multidisciplinary team).
- Patients with pulmonary compromise require long rest periods during therapy sessions.
- Patients requiring gait training with or without external assistance.

The physiotherapeutic intervention will be carried out according to the Physiotherapy Intervention protocol for critically ill patients at the Fundación Santa Fe de Bogotá (Code: AMB-REHF-PT-020).

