### **Physiotherapeutic Intervention**

According to the Speech Therapy care model in the ICU of the Hospital Universitario de la Fundación Santafé de Bogotá (FSFB), a patient begins intervention when the attending physician requests a consultation with Speech Therapy. Speech therapists conduct the evaluation and initiate the treatment plan.

As part of the SECEC-2023-129 project, there will be two intervention groups: early multimodal therapy and late multimodal therapy. Early Multimodal Therapy: This will be initiated within the first 24 hours following the intubation of a patient in the ICU.

Late Multimodal Therapy: This will be initiated according to the Speech Therapy care model for critically ill patients at the Fundación Santa Fe de Bogotá, i.e., when the attending physician requests a consultation with Speech Therapy.

Regardless of the group to which the patient is assigned, 2 sessions will be conducted daily (morning and afternoon) seven days a week, with each session lasting 15 to 30 minutes depending on the patient's RASS score.

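### None of the four Annex 1 therapy procedures carries the body's 72-hour minimum for the late arm, so the only intended difference between the arms is not secured

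*Protocol*

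**What the plan says.** **Body.** The Comparator row in section 3 reads: "Late multimodal therapy is defined as the initiation of multimodal therapy 3 days or more after the start of mechanical ventilation". It adds: "The comparator differs from the study intervention only in the moment", meaning the time from intubation to first therapy. Sections 6.1 and 6.5 both put the late start at 72 hours, and the last paragraph of section 6.3 describes the contrast as 24 against 72 hours. The early arm starts less than 24 hours after intubation.

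**Annex 1.** Section 6.11 calls this annex the operational plan of the trial. Each discipline procedure restates the two arms for this project and then gives its own start rule:

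- Respiratory therapy: "Late Multimodal Therapy: This will be initiated according to the Respiratory Therapy care model for critically ill patients", explained as "i.e., when the attending physician requests a consultation with Respiratory Therapy".
- Physiotherapy: "i.e., when the attending physician requests a consultation with Physical Medicine and Rehabilitation".
- Speech therapy (in a paragraph that is also headed as physiotherapeutic): "i.e., when the attending physician requests a consultation with Speech Therapy".
- Occupational therapy: "Early Multimodal Therapy and Late Multimodal Therapy: This will be initiated within the first 24 hours following the intubation of a patient". A separate paragraph, with no arm named, follows: "This will be initiated according to the standard management by occupational therapy in critical care", again explained as a physician's request.

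No sentence says which text prevails. The adherence criteria in section 6.9 do not mention start time.

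**The concern.** Both arms receive the same manoeuvres from the same disciplines, so the timing of the start is the whole experimental contrast. In the body that timing is assigned by randomisation and the clock. In Annex 1 the late-arm timing is a clinical decision taken after randomisation by an unblinded physician, with no earliest hour.

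A therapist who follows the annex could begin treating a late-arm patient well before 72 hours and be in line with that procedure while contradicting sections 3, 6.1 and 6.5. Each such patient moves the late arm towards the early arm. Section 6.9 decides who leaves the per-protocol analysis, and because it is silent on start time such a patient would not clearly count as a deviation there.

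**Working it through.** **1. Late-arm start rules side by side**

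| Place | Late-arm start | 72-hour minimum? |
|---|---|---|
| Section 3, Comparator | 3 days or more from start of ventilation | Yes, with no latest time |
| Section 6.1 | 72 h of ventilation | Yes |
| Section 6.3, last paragraph | contrast named as 24 h against 72 h | Yes |
| Section 6.5 | 72 h from intubation | Yes |
| Annex 1, respiratory therapy | on physician request | No |
| Annex 1, physiotherapy | on physician request | No |
| Annex 1, speech therapy | on physician request | No |
| Annex 1, occupational therapy | printed as within 24 h for both arms, then physician request with no arm named | No |

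The minimum stands in 4 places in the body and in 0 of 4 annex procedures.

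**2. Does the annex's other use of 72 hours supply the minimum?** No. The target-population lists in Annex 1 ask for ventilation beyond 72 hours. That is an entry criterion for both arms, not a start rule for one. It also disagrees with section 6.2, which asks for more than 24 hours. If it means time already ventilated, it cannot be combined with an early start inside 24 hours.

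**3. Guaranteed gap between the arms.** Let E be the early start and L the late start, in hours from intubation.

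- Body, L = 72 and 0 ≤ E < 24: L − E is more than 72 − 24 = 48 and at most 72 − 0 = 72.
- Body, L ≥ 72 (section 3): L − E is more than 48, with no maximum.
- Annex 1: L has no lower limit, so L − E has no guaranteed minimum. As an illustration, a request at hour 30 gives a gap of more than 30 − 24 = 6 hours and at most 30.

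**4. Side check on power (illustration only).** The plan gives no figure for this point, so there is none to reproduce. Section 6.3 gives means of 6.1 and 3.4 days, SDs of 1.40 and 1.25, and 31 per arm before the allowance for losses. Assume that a share f of the late arm starts as early as the early arm and then has the early-arm mean. The difference becomes 2.7 × (1 − f).

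- Pooled SD = √((1.40² + 1.25²)/2) = 1.327
- Standard error = 1.327 × √(2/31) = 0.337
- Power ≈ Φ(2.7(1 − f)/0.337 − 1.96), two-sided 0.05

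| f | Difference (days) | Power |
|---|---|---|
| 0 | 2.70 | >0.999 |
| 0.25 | 2.03 | >0.999 |
| 0.50 | 1.35 | 0.98 |
| 0.75 | 0.68 | 0.52 |
| 0.90 | 0.27 | 0.12 |

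The documents give no value for f. On the protocol's own inputs, power falls materially only if most of the late arm starts early.

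**The case against.** The best case for leaving the text alone has four parts.

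- **The body governs.** It points to Annex 1 for the content of the manoeuvres, while the arm definitions sit in sections 6.1 and 6.5. Section 6.11 requires training and an examination on the protocol, and a physician could time the request for 72 hours. This lowers the risk. But the annex procedures state arm-specific start rules for this trial, no sentence ranks the texts, and nothing tells the physician to wait. Section 6.5 also calls the manoeuvres part of standard care and lets both arms receive what they normally would.
- **Contamination would be seen.** Time from intubation to therapy is collected, and section 6.10 treats non-compliance above 20% as a threat to the trial. That detects early starts but does not prevent them, and the variable table records the time in days.
- **Occupational therapy.** A reader might infer that this procedure really starts both arms inside 24 hours. The text does not bear that out. The next paragraph gives the request rule, and a leftover drafting prompt shows the section is unfinished. A misplaced label is the likely explanation. Even so, that procedure contains no 72-hour minimum.
- **Late starts.** A reader might also blame Annex 1 for allowing starts long after 72 hours. That does not hold, because section 3 is equally open-ended. How late a start may be is a separate inconsistency within the body.

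**Conclusion.** The conflict is in the text and should be corrected. The body sets a 72-hour minimum for the late arm and no Annex 1 procedure repeats it. Three procedures use physician request, and the fourth most likely means to, under a garbled heading. A planned gap of more than 48 hours thus becomes no guaranteed gap for staff who work from the annex. An annex that was not updated to match the body is the probable cause.

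The size of the harm is unknown, because it depends on when physicians request consultations and the documents do not say. They do not support a claim that the contrast has been lost or that the trial is underpowered for this reason. The power figures rest on an assumed share f and on a comparison of means, whereas the primary analysis is a Cox model. What is established is that the contrast is undefined in the operational text. Separately, the body needs one answer on how late a start may be: sections 6.1 and 6.5 say at 72 hours, and section 3 says 3 days or more.

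**What to change.** 1. In all four Annex 1 procedures, state that the early arm starts within 24 hours of intubation, and that study therapy in the late arm starts at 72 hours and not before, whatever consultation has been requested.
2. State that endotracheal and oropharyngeal suction, oral hygiene and any clinically necessary airway care continue as routine care in both arms from intubation. This exemption is essential: the respiratory procedure lists suction and oral hygiene inside the session package, and section 6.5 does not separate them from study therapy.
3. Correct the occupational therapy heading so that each arm has its own rule.
4. Choose one late-start rule for sections 3, 6.1 and 6.5, including how late a start may be.
5. Name a late-arm start before 72 hours as a deviation in section 6.9.
6. Optionally, record time from intubation to therapy in hours and report it by arm.

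**Cost.** This takes a wording amendment for the ethics committee and a re-briefing of therapists. Sample size and analysis do not change. The real downside is that non-urgent study therapy requested before 72 hours is deferred in the late arm, overriding the request. Sections 6.1 and 6.5 already require that deferral.

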### Responsible Party, Frequency, and Location

Responsible Party: Respiratory Therapist

Frequency: According to medical orders and/or the discretion of the Respiratory Therapy professional

Location: Adult Intensive Care Unit (Third and fourth floors)

### Justification

The intervention processes of Occupational Therapy are directed towards preventing and mitigating the impact of acute pathological processes on the patient's autonomy and independence in their significant daily activities according to their history and occupational role, as well as preventing future deterioration in neurocognitive, sensorimotor, and psychosocial components (Ares Senra et al., 2014). In intensive care units, the focus will be on providing multisensory stimulation (emphasizing tactile, proprioceptive, visual, olfactory, and auditory inputs), cognitive stimulation, and promoting participation in meaningful daily life activities based on information received from the family, patient, and/or caregiver and reported in the clinical history, mediated by meaningful activities (Celis et al., 2014).

For patients with a RASS (Richmond Agitation-Sedation Scale) score of -3 or lower, multisensory stimulation activities of tactile, proprioceptive, vestibular, gustatory, auditory, and olfactory types will be performed, fully assisted by the therapist. These activities will correlate with simulated daily life tasks incorporating upper limb motor patterns (emphasizing primary patterns such as hand-head, hand-mouth, hand-homolateral, hand-contralateral, and hand-perineal) used in these tasks, as well as joint and skin care and protection. The intervention will be adjusted in an unimodal manner and subsequently multimodal according to the patient's tolerance in bed. Additionally, at the end of each session, the positioning of the appendicular segments (upper and lower limbs) will be ensured in functional resting angles to provide comfort and prevent contractures or edema. If a family member is present, they will be educated and given feedback on the therapeutic action performed and its objectives. Recommendations will also be provided to approach the patient and minimally participate in co-care, emphasizing tactile (skincare) and auditory (voice, audio clips of a maximum of 2 minutes continuous duration) stimuli.

For patients with RASS scores between -2 and -1, intervention processes will involve passive-assisted activities. In addition to sensory stimulation, emphasis will be placed on cognitive feedback processes for recognizing elements and generating daily tasks with instructional follow-up of a maximum of two commands, using integral movement patterns of reaching, grasping, voluntary or rudimentary releasing, and throwing with or without propulsion, emphasizing mid-frontal and lateral planes in bed.

When the patient has a RASS score of 0 to +1, the intervention will focus on the patient's participation in activities actively or autonomously with minimal support from the therapist according to the patient's tolerance. Greater emphasis will be placed on autonomy in daily tasks and the integration of sensory and cognitive commands of low/medium/high complexity according to the patient's evolution and responses. This includes the execution of upper limb patterns (primary,

secondary, and integral) previously worked on in all anatomical planes, both in bed/at the bedside and in a chair, according to the rehabilitation team's progress. The patient and family will be educated on the importance of promoting autonomy in self-care activities and seeking communication tools using pictograms or graphomotor acts with a board, providing support according to the patient's evolution and therapeutic process progress.

For patients with a RASS score of +2 or higher, therapeutic sessions will focus on behavioral and environmental (physical and family) modulation and fostering a connection with the environment through inhibitory multisensory stimulation activities combined with cognitive stimulation directed towards orientation and participation in the patient's significant tasks in an active-assisted manner in bed. Family members will be educated on continuous orientation processes with enriched sensory stimuli converging on a single task of visual, auditory, tactile, and proprioceptive types. All educational processes and recommendations will be provided in a theoretical-practical manner parallel to the intervention process.

### **Scope**

Patients selected for the research project: "Association between early multimodal therapy and days of mechanical ventilation in the intensive care unit of the Fundación Santa Fe de Bogotá: a randomized controlled clinical trial (SECEC-2023-129)."

### **Target Population**

#### **Inclusion Criteria:**

- Patients hospitalized in the adult intensive care unit of the Fundación Santa Fe de Bogotá require invasive mechanical ventilation through an endotracheal tube for more than 72 hours and are expected to continue for at least 24 hours.
- Barthel Index score of 70 or higher.

#### **Exclusion Criteria:**

- Patients requiring invasive mechanical ventilation through a tracheostomy or nasotracheal tube.
- Patients who have undergone any type of head and neck surgery.
- Cardiac arrest.
- Airway burn.
- Burns cover more than 50% of the body's surface area.
- Patients with chronic obstructive pulmonary disease (COPD).
- Patients referred from another institution.

- Patients with demyelinating diseases or neuromuscular junction disorders.
- Patients requiring neuromuscular relaxation.
- Patients with a life expectancy of less than 180 days.
- Patients who, according to medical criteria, would not benefit from multimodal treatment.
- Patients not admitted to the ICU for the first time.
- Patients participating in other rehabilitation clinical trials.

